#### Secondary endpoint analysis

2.10.3

Exact Mann–Whitney U-tests will be used for hypothesis testing of group differences in the ordinal and continuous secondary endpoints using two-sided exploratory significance levels of 5%. *T*-tests will be used in case of normal distribution. No adjustment for multiple comparisons will be made due to the exploratory nature of these analyses. Descriptive statistics will be computed for each endpoint by the treatment arm.

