### Randomization and blinding

2.3

Participants will be randomized into three parallel groups at an allocation ratio of 1:1:1 (Figure 1). There will be two Fasudil treatment arms (low and high dosage) and one placebo arm. Allocation will be performed based on a computer-generated randomization list. All procedures will be performed double-blind (patient- and investigator blind). During the clinical trial, unblinding may only occur in the case of an emergency, where the choice of treatment depends on the study subject’s therapy assignment. Emergency envelopes for the unblinding of study participants are provided.

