### Study procedures

2.5

A total of six visits (V0-V5) will be performed (see Table 2). Informed consent will be obtained before any study-specific procedure. During the screening visit (V0), eligibility according to inclusion and exclusion criteria, medical history, vital signs, concomitant medication, height, and weight will be established. A physical examination will be complemented by assessment of modified Hoehn and Yahr scale (mHY) and laboratory tests for safety parameters. This visit may take place up to 42 days in advance to the start of the treatment period. At the beginning of the treatment period, a baseline visit will be performed (V1). At this stage, we will reconfirm the inclusion and exclusion criteria, assess baseline measurements of laboratory parameters, vital safety indicators, and symptom-related assessment scales. These scales include the MDS-Unified PD Rating Scale I-IV (MDS-UPDRS), PD Quality of Life Scale (PDQ-8), PD Non-Motor Symptom Questionnaire (NMSQuest), Montreal Cognitive Assessment (MoCA), Beck’s Depression Inventory-II (BDI-II), and Global Impression of Improvement score (CGI-I [clinician], PGI-I [patient]). Participants will start intake of IMP in the evening after V1 and continue for 22 days. On the morning of day 22 the last dose should be administered at the study site. Safety parameters (laboratory measures and vital signs) will be assessed at all study related visits. These are on day 10 (±2 days; V2) and day 22 (−2 days; V3), during the treatment period, as well as day 36 (±3 days; V4) and 50 (±3 days; V5) during the washout period. At visits V2 and V3, tolerability will be recorded. Symptomatic efficacy will be assessed during treatment period (V2: subset of scales: MDS-UPDRS, subscales III and IV, NMSQuest, PGI-I, CGI-I), on the last day of treatment (V3), and after the wash-out phase (V5). We will collect biomaterials, including blood, cerebrospinal fluid (CSF), and tear fluid, for the purpose of establishing the pharmacokinetics of oral Fasudil and its active metabolite, Hydroxyfasudil. Additionally, these samples will be used to measure target engagement (ROCK activity) and for biobanking.

**Table 2 tab2:** Trial visit schedule.

Visit item	V0 screening	V1 BL	V2	V3	V4	V5
Day (d)	0	1	10	22	36	50
Permitted delta in days (±) to V1	−42	0	±2	−2	±3	±3
IMP orally 2x/d, on day 1 and day 22 1x/d		x	x	x		
*Screening assessment/randomization*						
Patient information and informed consent	X					

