#### Secondary outcomes

2.6.2

The occurrence of intolerance (termination of treatment because of treatment-related AE; time frame: from V1 to V3) and the occurrence of self-reported and pre-defined (laboratory, vital signs) treatment-related SAEs (from V1 to V3 and V1 to V5) will be assessed alone as two separate secondary outcomes. Furthermore, the symptomatic efficacy of oral Fasudil will be assessed as change of MDS-UPDRS (part I to IV from V1 to V3 and V1 to V5; part I and II from V1 to V3 and V1 to V5; part III and IV from V1 to V2, V1 to V3, and V1 to V5), the change of PDQ-8 (from V1 to V3 and V1 to V5), the change of NMSQuest (from V1 to V2, V1 to V3, and V1 to V5), the change of MoCA (from V1 to V3 and V1 to V5), the change of BDI-II (from V1 to V3 and V1 to V5), and the CGI-I/PGI-I (at V2, V3, and V5).

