### Sample size calculation

2.9

Expected probability for occurrence of the composite endpoint in the placebo arm is 5% at end of clinical trial. The two Fasudil arms are expected to reach about 12% each (according to the summary of product characteristics [SmPC] of Eril). A non-inferiority margin of 25% for the difference between Fasudil and placebo will be used based on data from previously published trials showing rates of discontinuation and severe adverse events of up to ~25% in patients treated with drugs that are in current clinical use for PD. For example, increased mortality was observed under selegiline/levodopa treatment (Lees, 1995), while side-effects (e.g., somnolence, dizziness, nausea) resulted in discontinuation in pramipexole-treated patients (Nissen et al., 2012; Schapira et al., 2013; Wang et al., 2017). Both drugs are in current use for PD. We thus consider a non-inferiority margin of ~25% as clinically and ethically acceptable for a drug that can have potentially disease-modifying properties and symptomatic effects. The two Fasudil arms will be tested against placebo in a hierarchical order, starting with the lower dose. This sequential procedure does not necessitate adjustment of the alpha level for multiple testing (Committee for Proprietary Medicinal Products (CPMP), 2002). According to the procedure no confirmatory claim can be based on the second test if the first test did not reach statistical significance. The significance levels are therefore each set to 10%, resulting to an overall type-I error of 10%. This error level was chosen in concordance with the recommendation of the European Medicines Agency (Committee for Medicinal Products for Human Use (CHMP), 2005). Given the aforementioned expected event rates, the non-inferiority margin and the alpha level of 10%, the sample size in each group needs to be 22 for a one-sided two-group test of proportions to reach a power of 80% to reject the null hypothesis that Fasudil is inferior to placebo in terms of its composite primary endpoint (calculated by nQuery Advisor V7.0, Statcon GmbH, Witzenhausen, Germany). A total of 3 × 25 = 75 patients are included in order to account for possible dropouts (for reasons other than intolerance; 12% drop-out).

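### The efficacy changes are compared without the V1 score as a covariate, and a normality-dependent choice of test leaves open which effect is reported

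*Protocol article*

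**What the plan says.** Section 2.6.2 (Secondary outcomes) states that "the symptomatic efficacy of oral Fasudil will be assessed as change of MDS-UPDRS" from V1 to later visits. PDQ-8, NMSQuest, MoCA and BDI-II are likewise defined as changes from V1. CGI-I and PGI-I are taken as values at V2, V3 and V5. Section 2.5 (Study procedures) says that V1 will "assess baseline measurements of laboratory parameters, vital safety indicators, and symptom-related assessment scales", so the baseline values of the change-scored scales are available.

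Section 2.10.3 (Secondary endpoint analysis) names the exact Mann-Whitney procedure, which "will be used for hypothesis testing of group differences in the ordinal and continuous secondary endpoints using two-sided exploratory significance levels of 5" per cent, and says that t-"tests will be used in case of normal distribution". It gives no covariate and no criterion for normality. It adds: "No adjustment for multiple comparisons will be made due to the exploratory nature of these analyses". Descriptive statistics are promised for each arm.

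The trial has three arms at 1:1:1. Section 2.9 says: "A total of 3 × 25 = 75 patients are included in order to account for possible dropouts". That number is derived only from the binary safety and tolerability endpoint.

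**The concern.** Two features of Section 2.10.3 deserve attention, and both are things the text fixes rather than leaves out.

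- **No covariate.** A raw change score forces the slope of follow-up on baseline to be 1. When the true slope is smaller, the change score carries avoidable noise and over-corrects for chance baseline differences. ANCOVA estimates the slope from data that are already collected.
- **Test chosen from the data.** A t-test addresses a difference in means; a Mann-Whitney test addresses a shift in ranks. If the observed distribution decides between them, the quantity reported can differ from scale to scale, visit to visit and dose to dose.

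Symptomatic efficacy is a named objective in Section 2.1, and the closing discussion expects the trial to prepare longer studies that assess it. With 25 patients per arm and no sample-size provision for efficacy, there is little precision to give away. A between-arm estimate with its uncertainty would be the useful product, and the plan promises only tests and per-arm summaries.

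**Working it through.** **The plan's own sample size.** Section 2.9 gives event rates of 5% and 12%, a margin of 25 points, one-sided alpha 10% and power 80%.

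n = (1.2816 + 0.8416)² × (0.05×0.95 + 0.12×0.88) / (0.25 − 0.07)² = 4.508 × 0.1531 / 0.0324 = 21.3, so 22 per group. Then 22 / 0.88 = 25 per group and 3 × 25 = 75. The stated figures reproduce. They concern the primary endpoint and say nothing about precision on the efficacy scales.

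**Precision of the efficacy comparison.** Assume equal SD σ at V1 and follow-up and correlation r. Neither is in the document, so r is shown over a range.

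- Variance of a raw change: 2σ²(1 − r).
- Residual variance after adjustment for V1: σ²(1 − r²).
- Ratio: (1 − r²) / [2(1 − r)] = (1 + r)/2.
- Allowance for estimating the slope with n per arm: about (2n − 3)/(2n − 4), which is 47/46 = 1.022 at n = 25.

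The power column takes an effect for which the raw-change t-test would have 80% power (two-sided 5%).

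| r (assumed) | (1+r)/2 | with allowance, n = 25 | equivalent n per arm | power after adjustment |
|---|---|---|---|---|
| 0.5 | 0.75 | 0.77 | 33 | 89% |
| 0.7 | 0.85 | 0.87 | 29 | 85% |
| 0.8 | 0.90 | 0.92 | 27 | 83% |
| 0.9 | 0.95 | 0.97 | 26 | 81% |
| 0.95 | 0.975 | 1.00 | 25 | 80% |

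With 22 evaluable per arm, the power after adjustment is 89%, 85% and 81% at r = 0.5, 0.7 and 0.9.

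**Simulation.** 4,000 trials per setting, 25 per arm, using the same effects. The switch was modelled as a Shapiro-Wilk test at 5% in each arm, which is an assumption because the plan gives no criterion.

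| Power | r = 0.5 | r = 0.7 | r = 0.9 |
|---|---|---|---|
| Normal: Mann-Whitney on change | 76% | 76% | 75% |
| Normal: t-test on change | 79% | 78% | 78% |
| Normal: ANCOVA | 87% | 84% | 79% |
| Skewed errors: Mann-Whitney on change | 87% | 91% | 93% |
| Skewed errors: ANCOVA | 87% | 83% | 81% |

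Type I error with the switch was 5.3% for normal data and 5.1% to 5.8% for skewed errors, against a nominal 5%.

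**Does the choice of test matter to the result?** With normal data, 19 and 21 patients per arm, an effect of 0.6 SD and r from 0.5 to 0.8 (all illustrative assumptions), the t-test and Mann-Whitney test fell on opposite sides of 5% in about 5% to 8% of trials. Disagreement was more frequent with skewed data.

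**The case against.** The strongest reply is that an unadjusted comparison of changes is valid under randomization. The analyses are secondary and declared exploratory, the trial is sized for another endpoint, and a rank test is a defensible default for bounded or ordinal scales. All of that stands. It makes this a matter of efficiency and clarity, not of validity.

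The size of the gain is also open. Patients must be non-fluctuating and stable on medication, and V3 is only about three weeks after V1, so a high correlation is plausible. At 0.9 or above, adjustment buys almost nothing. Linear ANCOVA is not uniformly better either: with skewed errors, Mann-Whitney on change had more power at r = 0.7 and 0.9. That argues against imposing a linear model on every scale, but not against using V1, since a rank-based analysis can also adjust for it.

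Several stronger readings are tempting but unsupported:

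- **That baseline is thrown away.** It is not; Section 2.6.2 subtracts it.
- **That the switch inflates false positives.** The simulation shows an error rate close to 5%. The article does not say that a formal normality test will be used, nor on which data, and such detail may sit in the analysis plan.
- **That nothing usable for planning will be reported.** Per-arm descriptive statistics are promised, and a crude difference can be formed from them. What is not stated is a between-arm estimate with a confidence interval.
- **That the plan's assumptions imply 22.6% missing V3 scores on Fasudil (1 − 0.88×0.88) and 16.4% on placebo (1 − 0.95×0.88).** This counts every composite event as a missing score. The composite includes serious events without discontinuation, and nothing says that patients who stop treatment have no V3 assessment. The stated drop-out is 12%.

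**Conclusion.** The point holds as a modest improvement worth making. Section 2.10.3 fixes unadjusted two-group tests for five change-scored instruments whose V1 values are collected. Using V1 as a covariate would cut the variance of the treatment difference by about 23% at r = 0.5, 13% at 0.7, 8% at 0.8 and 3% at 0.9, with no gain at 0.95. These figures assume equal SDs, 25 per arm and a linear relation with normal errors; the correlation itself cannot be taken from the document.

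Separately, the normality-dependent switch leaves undefined which effect is estimated for each scale and visit, although it does not materially disturb the type I error. CGI-I and PGI-I are not changes from baseline, so the covariate point does not reach them. The consequence is confined to exploratory secondary endpoints; the non-inferiority analysis is untouched.

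**What to change.** In Section 2.10.3, and in the analysis plan to match:

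- Name one baseline-adjusted analysis for each change-scored scale before unblinding: ANCOVA of change on arm with the V1 value as covariate, or, where skewed or bounded scores are expected, a rank-based or proportional-odds analysis with V1 as covariate.
- Report the adjusted difference with a 95% CI for each dose against placebo, and keep the exploratory label.
- Keep Mann-Whitney for CGI-I and PGI-I, and as a sensitivity analysis for the other scales.
- Delete the sentence that makes the t-test conditional on normality.

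The cost is a change of wording and one degree of freedom per model. No additional data or visits are needed. The real downside is that linear ANCOVA can lose power to a rank test when changes are strongly skewed, which is why the form should be chosen scale by scale in advance.

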## Discussion

3

### Rationale for the choice of Fasudil

3.1

Fasudil, a ROCK-inhibitor, has been developed as a vasodilatory drug and is licensed for the treatment of vasospasms after intracranial hemorrhage. There is strong preclinical evidence that Fasudil can be beneficial for different neurodegenerative diseases. In preclinical models of PD, ROCK-inhibition by Fasudil displays promising properties to counteract PD-related pathology on different levels: Fasudil was shown to (1) counteract alpha-synuclein aggregation, a central neuropathological hallmark of PD (He et al., 2016; Tatenhorst et al., 2016), (2) enhance dopaminergic survival in the substantia nigra and maintain striatal dopaminergic terminals, the neuroanatomical basis of motor dysfunction in PD (Tönges et al., 2012; He et al., 2016), (3) reduce neuroinflammation, which is associated with neurodegeneration and neurotoxicity (He et al., 2016), and (4) enhance neuroprotective Parkin-mediated mitophagy (Moskal et al., 2020). Fasudil treatment resulted in significant improvement in motor symptoms in rodent models of PD (He et al., 2016; Tatenhorst et al., 2016), improved cognition in a transgenic mouse model of Alzheimer’s disease (Yan et al., 2021), and prolonged survival in a Parkin drosophila model (Moskal et al., 2020). Furthermore, Fasudil has shown dopaminergic effects in mouse models, suggesting that it could also have symptomatic effects in patients (Sortwell et al., 2013; Lopez-Lopez et al., 2020).

### Rational for dose selection and trial design

3.2

Whereas in the licensed indication of Fasudil, the acute and vasoactive effect of the drug is sought for, and a three times daily regimen is required, treatment in chronic neurodegenerative disorders requires long-term application of the drug. In this clinical trial, the treatment period of 22 days followed by a wash-out phase of 28 days has been chosen to assess symptomatic effects and to establish a safety profile of an administration regime suitable for potential long-term treatment (Holloway et al., 2004). Oral application of Fasudil is expected to result in better treatment adherence long-term than intravenous application. Fluctuating patients are excluded from the clinical trial to not obscure symptomatic effects. An additional efficacy endpoint after 10 days will evaluate early symptomatic effects both in motor and nonmotor domains of PD in a subset of assessments. In this clinical trial, the licensed cumulative dosage of 3 × 30 mg/day (IV) for 14 days was transformed to 2 × 30 mg/day IV (corresponding to 2 × 44 mg/day *per os*) for 21 days, therefore adapting to a regime eligible for long-term treatment, while considering the approved cumulative dosage. This calculation is based on findings from a pharmacokinetic study, in which treatment with 45 mg Fasudil IV reached a mean peak level of 22.8 ng/mL Hydroxyfasudil, the active metabolite of Fasudil, in CSF (Hanada et al., 2005). Considering linear pharmacodynamics, peak levels after application of 15 or 30 mg Fasudil IV should be expected to be ~7.5 or 15 ng/mL, respectively, in the CSF. This corresponds well to the levels of Hydroxyfasudil, which were measured in mouse CSF (8.8 ng/mL) after oral treatment with Fasudil and resulted in beneficial effects on histological and behavioral parameters in multiple independent mouse models of PD (Tönges et al., 2012; Tatenhorst et al., 2016). To administer Fasudil as oral formulation, we performed an oral bioavailability trial (SAFE-ROCK, Eudra-CT-Nr.: 2019-001805-26) that showed excellent bioavailability of oral Fasudil compared to Fasudil IV. The area under the curve of Hydroxyfasudil concentrations was ~45% higher after the administration of the intravenous treatment compared to the oral treatment (Wolff et al., in revision). Therefore, in the present trial, two dosages adapted to this difference of 45% are used: 22 and 44 mg *per os* corresponding to 15 and 30 mg IV. Placebo was chosen as comparator because no gold-standard disease-modifying treatment for Parkinson’s disease exists to date. Because Fasudil has a slightly bitter taste, the placebo solution is supplemented with a bittering agent. Quinine dihydrochloride solution is frequently used in clinical trials to generate a bitter placebo solution. To this, 12.5 mg quinine dihydrochloride per placebo dosage are used, which is not pharmacologically active in this dosage.

### Risk and benefit analysis

3.3

There is an ongoing need to develop disease modifying therapies for PD (Lang and Espay, 2018; McFarthing et al., 2023). Current treatment is limited to reduce symptoms but cannot prevent continuous symptomatic deterioration and progressing neuropathology. It is therefore an important aim to develop effective treatments that can stop or slow the course of the disease. Over the last decades, many therapeutics have demonstrated promising effects *in vitro* and animal models, but no effect could yet be translated into clinical disease-modifying effectiveness. Reasons for this are multifaceted and may relate to insufficient representation of disease pathology by available models, drug-related pharmacokinetic differences in humans, inadequately designed trials with too short follow-up periods as well as insufficient measures for long-term disease progression (Vijiaratnam et al., 2021). This makes development of disease modifying therapies time consuming and expensive. Therefore, drug repurposing – the evaluation of an already approved medication in a new disease or condition – can play a critical role in this development (Fletcher et al., 2021). Fasudil has been marketed for more than 25 years with a promising safety and tolerability profile (Suzuki et al., 2007). Most of its safety data originates from acute treatment over short time (14 days), yet Fasudil has been tested for longer treatment periods of up to 12 weeks in exploratory settings of vascular diseases (Vicari et al., 2005; Fukumoto et al., 2013). In this setting, the most common side effects were mild to moderate and did not occur significantly more frequent than in the placebo group. However, intracranial hemorrhage is listed as a side effect of treatment with Fasudil, which is most likely related to the indication of treatment instead of Fasudil itself. Bleeding relapse after intracerebral hemorrhage occurred in up to 30% within 1 year (Passero et al., 1995) and in 4% after an aneurysmal subarachnoid hemorrhage (Starke and Connolly, 2011), which is even more frequent than findings in Fasudil-treated patients where hemorrhages occurred in <2% (Suzuki et al., 2007). However, to exclude conditions that predispose for the occurrence of intracranial hemorrhages, patients with intracerebral aneurysms will be excluded from the current trial and those with a positive family history for aneurysms need to present an unremarkable cerebrovascular imaging result. The administration of placebo in our study population is acceptable since both placebo and Fasudil are given as add-on to the routine symptomatic therapy. On October 2nd, 2022, a search was performed in www.drugbank.ca (global drug properties) to identify known interactions between Fasudil and anti-parkinsonian drugs used for the treatment of early PD. No interaction was determined for Fasudil and levodopa/benserazide, levodopa/carbidopa, ropinirol, pramipexole, piribidil, entacapon, opicapone, amantadine, rasagiline, and selegiline. Fasudil is not listed on the Drug Interactions Flockhart Table™ of inhibitors or inducers of P450.^4^ The safety of the trial participants is of primary importance, and risks associated with the clinical trial participation have been weighed against the anticipated benefit for the clinical trial participants. All clinical data available so far provide reasonable evidence that Fasudil is eligible and safe for treatment in patients but data in PD patients are currently lacking. Based on preclinical findings, short-term symptomatic improvement seems possible. Although long-term benefits for the participants may be limited, they cannot be ruled out. Taken together, the benefits outweigh the risks.

Concluding, ROCK-PD is investigating safety, tolerability, and symptomatic efficacy of the ROCK-inhibitor Fasudil, which is a promising, potentially disease modifying molecule for PD. Based on the safety data and pharmacokinetic profile of Fasudil determined in this study, future clinical trials can be planned. Most importantly, this clinical trial can lay grounds for studies with a longer treatment duration to evaluate both symptomatic efficacy and disease modifying properties.

## Ethics

4

This clinical trial will be conducted in accordance with the current ICH-GCP-guidelines and Declaration of Helsinki. Written informed consent will be obtained from all participants. Prior to study start the following documents were obtained:

Approval of ethics committees (lead ethics committee at TU München [2022-443-Af-NP] and local ethics committees).Approval of national competent authority: Bundesamt für Arzneimittel und Medizinprodukte (BfArM).Notification to applicable regional authorities.Trial insurance.

Irrespective of the study outcome, the results will be disseminated through www.clinicaltrials.gov, in a peer-reviewed, international journal, and national and international conferences respecting the privacy of the participants. A lay summary of the results will be available on the study website.

